# Connect MDS/AML: design of the myelodysplastic syndromes and acute myeloid leukemia disease registry, a prospective observational cohort study

**DOI:** 10.1186/s12885-016-2710-6

**Published:** 2016-08-19

**Keywords:** Myelodysplastic syndromes, Acute myeloid leukemia, Idiopathic cytopenia of undetermined significance, Registry, Treatment patterns, Clinical outcomes, Patient-reported outcomes, Biomarkers, Clonal hematopoiesis of indeterminate potential (CHIP)

## Abstract

**Background:**

Myelodysplastic syndromes (MDS) and acute myeloid leukemia (AML) are myeloid neoplasms in which outgrowth of neoplastic clones disrupts normal hematopoiesis. Some patients with unexplained persistent cytopenias may not meet minimal diagnostic criteria for MDS but an alternate diagnosis is not apparent; the term idiopathic cytopenia of undetermined significance (ICUS) has been used to describe this state. MDS and AML occur primarily in older patients who are often treated outside the clinical trial setting. Consequently, our understanding of the patterns of diagnostic evaluation, management, and outcomes of these patients is limited. Furthermore, there are few natural history studies of ICUS. To better understand how patients who have MDS, ICUS, or AML are managed in the routine clinical setting, the Connect MDS/AML Disease Registry, a multicenter, prospective, observational cohort study of patients newly diagnosed with these conditions has been initiated.

**Methods/Design:**

The Connect MDS/AML Disease Registry will capture diagnosis, risk assessment, treatment, and outcomes data for approximately 1500 newly diagnosed patients from approximately 150 community and academic sites in the United States in 4 cohorts: (1) lower-risk MDS (International Prognostic Scoring System [IPSS] low and intermediate-1 risk), with and without del(5q); (2) higher-risk MDS (IPSS intermediate-2 and high risk); (3) ICUS; and (4) AML in patients aged ≥ 55 years (excluding acute promyelocytic leukemia). Diagnosis will be confirmed by central review. Baseline patient characteristics, diagnostic patterns, treatment patterns, clinical outcomes, health economics outcomes, and patient-reported health-related quality of life will be entered into an electronic data capture system at enrollment and quarterly for 8 years. A tissue substudy to explore the relationship between karyotypes, molecular markers, and clinical outcomes will be conducted, and is optional for patients.

**Discussion:**

The Connect MDS/AML Disease Registry will be the first prospective, observational, non-interventional study in the United States to collect clinical information, patient-reported outcomes, and tissue samples from patients with MDS, ICUS, or AML receiving multiple therapies. Results from this registry may provide new insights into the relationship between diagnostic practices, treatment regimens, and outcomes in patients with these diseases and identify areas for future investigation.

**Trial registration:**

Connect MDS/AML Disease Registry (NCT01688011). Registered 14 September 2012.

**Electronic supplementary material:**

The online version of this article (doi:10.1186/s12885-016-2710-6) contains supplementary material, which is available to authorized users.

## Background

Myelodysplastic syndromes (MDS) are a heterogeneous group of clonal myeloid malignancies characterized by ineffective hematopoiesis, peripheral blood cytopenias, and a propensity to transform into acute myeloid leukemia (AML) [1–3]. AML, which can arise de novo or secondary to prior myeloproliferative neoplasms or MDS, is defined by ≥ 20 % myeloid blasts in the marrow or blood, or the presence of specific cytogenetic abnormalities [4]. In the elderly, AML and MDS tend to have similar presentation with cytopenias and associated clinical manifestations of these cytopenias, including infection, bleeding, and the poor oxygen-carrying capacity characteristic of anemia [2, 5]. MDS and AML are classified using World Health Organization criteria based on blood counts, morphological criteria, and cytogenetic data [6, 7]. Some patients with persistent cytopenia(s) may not meet the minimal diagnostic criteria for MDS, yet no other diagnosis is apparent [8]. These patients are said to have idiopathic cytopenia of undetermined significance (ICUS) [8]. Unlike monoclonal gammopathy of undetermined significance, a clonal state that is a precursor to multiple myeloma or other plasma cell neoplasms, ICUS is not a clonal disorder by definition; if a clonal mutation in a myeloid neoplasia–associated gene is present, the patient is instead said to have clonal hematopoiesis of indeterminate potential (CHIP) [9]. Although some patients with ICUS may eventually develop MDS or AML, the proportion that do is unknown as there is a lack of natural history studies of this condition [9–11].

Although MDS, ICUS, and AML can occur at any age, they are most common in older patients. In the United States, the median age at diagnosis of MDS and AML is approximately 70 years, although exact estimates vary [12, 13]. Less is known regarding the epidemiology of ICUS, although the median age reported in the few existing studies ranges from 61 to 69 years [11].

Because of varying criteria for diagnosis, omission of MDS in cancer registries until recently, and incomplete evaluation of many elderly patients with mild cytopenias, it has been difficult to accurately assess the incidence and prevalence of MDS [2, 14, 15]. Based on US Medicare claims data, it is estimated there may be ≥ 75 new cases of MDS per 100,000 people aged ≥ 65 annually in the United States, making MDS one of the most common hematologic malignancies [2, 15, 16]. AML is the most common acute leukemia in the United States, with approximately 20,000 new cases annually [12]. The incidence of ICUS remains unclear.

MDS treatment recommendations are based on individual patient characteristics and disease risk, which can be assessed using one of several prognostic scoring systems [17], such as the widely used 1997 International Prognostic Scoring System (IPSS). Patients with asymptomatic lower-risk (IPSS low/intermediate-1 [Int-1] risk) MDS are often monitored using a “watch and wait” approach, without specific therapy [18]. Patients with symptomatic lower-risk MDS are generally treated with low-intensity therapies such as supportive care (ie, transfusion support or erythropoiesis-stimulating agents) or lenalidomide, whereas those with higher-risk (IPSS int-2/high risk) MDS are often treated more intensively with disease-modifying therapy, including the DNA hypomethylating agents (HMAs) azacitidine or decitabine, cytotoxic chemotherapy, or allogeneic stem cell transplant [17]. However, except in younger, healthier patients who can potentially be cured with allogeneic stem cell transplant, MDS therapy is largely palliative, and many questions remain regarding the optimal management of patients with MDS [2].

The IPSS was revised (IPSS-R) in 2012 to improve risk stratification [19]. The IPSS-R includes more parameters than the IPSS and adds a fifth intermediate risk category that doesn’t fall cleanly into lower or higher risk, which may make this fifth category challenging for physicians to incorporate into routine clinical practice [2, 17, 19]. Additionally, a modification of the IPSS-R that incorporates mutational data was recently proposed, providing enhanced predictive power in patients with MDS across the course of the disease, regardless of treatment history [20]. Although the IPSS-R was designed to improve prognostic classification, prospective studies detailing how the IPSS-R is being used in clinical practice and what effect this has on real-world treatment decisions and outcomes have yet to be conducted.

AML treatment recommendations are largely based on age, with intensive chemotherapy and transplant generally reserved for patients less than 70 years of age [5]. Patient fitness is also taken into account when determining eligibility for intensive treatment and transplant [21], and this often requires clinicians to make difficult judgments. Treatment options for older patients with AML who are not eligible for intensive treatment are limited and, outside of a clinical trial, typically include HMAs, low-dose cytarabine, and supportive care [5, 12]. Outcomes in older patients with AML remain dismal, with a 5-year survival rate of 5 % in patients > 65 years of age in the United States, which lags behind the 38 % 5-year survival rate in patients < 65 years of age [5, 12].

Although various guidelines exist for the treatment of patients with MDS and AML, such as those of the National Comprehensive Cancer Network (NCCN) or the European LeukemiaNet [17, 21–23], patterns of treatment and clinical outcomes in patients with MDS or AML outside of clinical trials are poorly characterized. Treatment decision-making can be complex and challenging, especially for elderly patients who may have comorbid conditions and poor performance status [5, 24]. Moreover, a recent survey of physicians treating patients with MDS indicated that they frequently did not adhere to NCCN guidelines for length of treatment [25].

There are currently no specific treatments for ICUS other than addressing factors contributing to cytopenias when identified, and it is recommended that patients be monitored with regular follow-up hematologic assessments to surveil for progression to an overt myeloid neoplasm [11]. No large observational studies have been performed to date to inform best clinical practices and to understand long-term outcomes in patients with ICUS [9, 11].

There are currently gaps in the knowledge of MDS, ICUS, and AML with regard to diagnostic trends, prognostic categorization, long-term treatment patterns, and clinical and health-related quality of life (HRQOL) outcomes. Moreover, data from patients enrolled in clinical trials may not apply to patients treated outside of a trial, such as those who may lack sufficient resources to travel to participate in a trial or who are excluded from such trials due to poor performance status and multiple comorbidities [5, 26, 27]. The Connect MDS/AML Disease Registry (Clinicaltrials.gov Identifier NCT01688011) is a multicenter, prospective, observational cohort study of patients with newly diagnosed MDS, ICUS, or AML in the United States. This registry aims to acquire robust data that will be representative of these patient populations in the United States. It is designed to capture patterns of diagnosis, risk assessment, and treatment of MDS, ICUS, and AML as well as clinical and patient-reported outcomes (PROs). This registry represents an opportunity to document key variables affecting treatment decisions and clinical outcomes in MDS, ICUS, and AML and to provide new insight into these heterogeneous diseases. The primary objectives of the disease registry are to:Describe the current and evolving patterns of diagnosis, prognosis, evaluation, treatment, clinical monitoring, and outcome measures;Compare actual clinical practice patterns in both community and academic settings with existing management guidelines (eg, NCCN);Describe treatment patterns and the associated short- and long-term outcomes in non-del(5q) patients and in del(5q) patients with or without additional cytogenetic abnormalities, including response, safety, disease progression, and survival;Summarize PROs (eg, HRQOL) and health economics and outcomes research (HEOR) and their association with patient characteristics, treatment regimens, and clinical outcomes.

The disease registry study plan also includes a correlative substudy designed to identify molecular markers and evaluate their potential impact on prognostication and/or treatment outcomes.

## Methods/Design

The Connect MDS/AML Disease Registry was designed collaboratively by 2 scientific steering committees (SSCs) composed of academic and community-based practitioners in MDS (SSC-MDS) and AML (SSC-AML) in partnership with Celgene Corporation. The SSCs include experts in molecular and correlative research, as well as HRQOL, and are responsible for managing the study with guidance and review by Celgene Corporation.

### Setting

Patients will be enrolled at approximately 150 sites in the United States. Hematologists or oncologists experienced in the treatment of MDS, ICUS, or AML expressing an interest in participating in the disease registry will be evaluated as site principal investigators. Study investigators must maintain a practice with enough potential patients to achieve the quarterly enrollment target, and have adequate staff available for coordinating the study and conducting daily research activities. To best capture the distribution of routine clinical practice settings in which patients are typically treated, approximately 70 to 80 % of the sites will be community-based clinics and 20 to 30 % will be academic institutions (defined as affiliated with a medical school).

### Sample size

Approximately 1500 patients with MDS, ICUS, or AML will be enrolled into 4 main cohorts (Fig. 1). The sizes of the cohorts were chosen to ensure adequate representation to address the critical objectives of the registry. The first cohort consists of 700 patients with lower-risk MDS, classified as IPSS low and int-1 risk, and is divided into subcohorts of patients with del(5q) (n = 250) and without del(5q) (n = 450). One of the objectives of the del(5q) cohort is to describe treatment outcomes in these patients. Currently, the only approved treatment specific to the del(5q) subgroup is lenalidomide, and approximately 50 % of patients with del(5q) continue past 3 cycles of therapy. Therefore, the expectation is that 125 patients will be on lenalidomide for more than 3 cycles. For the 250 del(5q) patients with an expected response rate of 57 % with a 10-mg dose, based on the MDS-003 and MDS-004 studies, the 2-sided 95 % confidence interval for this estimate is 0.51 to 0.63. For the 450 non-del(5q) patients, based on the MDS-005 study, > 60 % of patients, or approximately 270 patients, are expected to complete 4 cycles of therapy. With an expected response rate of 27 %, the 2-sided 95 % confidence interval is 0.23 to 0.31 and 122 patients are expected to respond, providing enough patients to explore predictors of response. The second cohort consists of patients with higher-risk MDS (n = 200), classified as IPSS int-2 or high risk. Two hundred patients should be an adequate sample size to describe diagnostic patterns and treatment effectiveness in this cohort. The third cohort consists of patients with ICUS (n = 200). No sample size estimation was done for this group since it is viewed as exploratory. The fourth cohort consists of patients with AML aged ≥ 55 years (n = 400). The age criterion was selected for patients with AML because of the complexities of treating older patients due to age-related comorbidities and increased vulnerability to therapeutic toxicities [5, 21, 26]. A sample size of 400 patients should be sufficient to characterize the complexities of treating these older patients.

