### Data collection

Patient data will be entered into the electronic data capture (EDC) system at screening, enrollment (ie, baseline), and approximately quarterly intervals throughout the duration of a patient’s participation. All decisions regarding patient care (treatment, response assessment, etc.) will be determined by the study clinician, as the disease registry is non-interventional. The EDC will capture clinical outcomes, and patients will be followed for 8 years or until early study termination, patient withdrawal, or death. For patients with MDS treated with supportive care alone, the median survival ranges from 0.4 years in the high-risk IPSS group to 5.7 years in the low-risk IPSS group [28]. For patients with AML, the 5-year survival rate is 27 %, whereas for older patients (75–84 years), the 1-year survival is 15 % [12, 29]. Thus, the 8-year follow-up period is an adequate length of time to acquire robust data on both the short- and long-term outcomes of patients with MDS, ICUS, and AML. Follow-up will continue regardless of whether patients remain on or discontinue treatment. The total study duration is approximately 11 years, including a 3-year screening and enrollment period and an 8-year follow-up period.

Information to be captured by the disease registry includes baseline characteristics, comorbidities, frailty evaluations, diagnostic testing results, treatment, clinical outcomes, HEOR, and HRQOL, as described in Table 1. Patient-reported HRQOL data will be collected using 2 instruments: the Functional Assessment of Cancer Therapy-Anemia (FACT-An), which assesses physical, social, family, emotional, and functional well-being, and fatigue- and anemia-related concerns [30] and the EuroQol Group 5-dimension, 3-level questionnaire (EQ-5D-3 L), which assesses mobility, self-care, usual activities, pain and discomfort, anxiety, depression, and overall health status [31]. All clinical outcomes will be assessed by the treating physician as would occur in routine clinical practice (Table 2) and captured using electronic case report forms.

**Table 1 Tab1:** Information and assessments captured by the Connect MDS/AML Disease Registry

Type of Assessment	Variables
Baseline descriptions	• Patient eligibility • Patient demographics and medical history • Prior malignancies • ECOG performance status • Clinical frailty scale • Adult comorbidity evaluation (ACE-27) • Current and concomitant medications

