### Data quality

Certain aspects of the disease registry were designed to mitigate potential biases that could affect data quality. To control for selection bias, all consecutive patients at each site who are diagnosed with MDS, ICUS, or AML and who are potentially eligible for the disease registry will be presented with the option of enrolling, until accrual is met. To ensure high-quality data collection, each site will participate in training specific to registries via investigator meetings, teleconferences, or webinars, and a site initiation visit via teleconference or webinar with United BioSource Corporation (UBC). Ongoing site support and continuing education will be provided throughout the duration of the study. Information bias will be prevented through the proper handling of missing data by the EDC system. A major advantage of using an EDC system for data collection is that it allows real-time, remote data quality control through edit checks and data queries that are automated based on validation rules programmed in advance. This eliminates the need for on-site monitoring, as the programmed validation rules will obtain immediate feedback if data are missing or unclear. For example, data fields will be programmed in a way that prevents leaving an entry blank, and error messages will be generated in real time if values entered outside of the preset range are detected.

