### Status of the registry

The first patient was enrolled in the disease registry on December 12, 2013. As of November 30, 2015, enrollment is 306 patients. There are currently 104 patients enrolled in the IPSS lower-risk MDS cohort (10 patients with del(5q) and 94 patients without del(5q)), 80 patients in the IPSS higher-risk MDS cohort, 0 patients in the ICUS cohort, and 121 patients in the AML cohort. There are currently 169 accepted study sites and 149 activated sites (Fig. 2).

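### The del(5q) size of 250, its 0.51 to 0.63 interval and the 125 patients past 3 cycles are not supported by the registry's own accrual within its 3-year enrolment period

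*Protocol article*

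**What the plan says.** Sample size: the lower-risk MDS cohort of 700 "is divided into subcohorts of patients with del(5q) (n = 250) and without del(5q) (n = 450". For del(5q) it continues "For the 250 del(5q) patients with an expected response rate of" 57 %, and the two-sided 95 % "confidence interval for this estimate is 0.51 to 0.63". About half of del(5q) patients are assumed to continue past 3 cycles, hence 125.

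Data collection: a total study duration of about 11 years, "including a 3-year screening and enrollment period and an 8-year follow-up period".

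Data quality: to control selection bias, enrolment is offered to "all consecutive patients at each site who are diagnosed with MDS, ICUS, or AML and who are potentially eligible" until the target is reached. The article does not say whether that means the subcohort, the cohort or the whole registry. It describes no enrichment for del(5q).

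Status of the registry: the first patient was enrolled on 12 December 2013. On 30 November 2015 there were 306 patients and 149 activated sites, against about 150 planned under Setting. On the lower-risk cohort: "There are currently 104 patients enrolled in the IPSS lower-risk MDS cohort (10 patients with del(5q) and 94 patients without del(5q").

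**The concern.** The target, the sampling rule, the enrolment period and the accrual counts stand in the same article and are not reconciled. The target needs more than one lower-risk patient in three to have del(5q); the registry is finding about one in ten. Slow recruitment alone might correct itself, but a case mix this far from the design share does not correct itself by opening more sites.

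Describing treatment outcomes in del(5q) patients is part of a primary objective, and this interval is one of only two precision figures in the sample-size section. A reader would expect a half-width of 0.06 and 125 patients past 3 cycles, when the data in hand point to several times that width and a small fraction of that number.

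**Working it through.** **Inputs.** Targets 250 and 450, response rate 0.57 and one half continuing past 3 cycles (Sample size); 36 months of enrolment (Data collection); 10 del(5q), 94 non-del(5q) and 306 patients in all, with both dates (Status of the registry). I assume the 36 months start with the first patient.

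**1. The plan's own figure.** Wald interval p ± 1.96·√(p(1−p)/n): 0.57 ± 1.96·√(0.57·0.43/250) = 0.57 ± 0.061, or 0.509 to 0.631. This reproduces 0.51 to 0.63. Also 250 × 0.5 = 125.

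**2. Case mix.** Design share 250/700 = 35.7 %. Observed share 10/104 = 9.6 %, exact 95 % CI 4.7 to 17.0 %. If the true share were 35.7 %, the binomial probability of 10 or fewer in 104 is about 1 in 10⁹. At the observed share, 250 del(5q) patients need 250/(10/104) = 2600 lower-risk patients (1473 to 5310 over the exact limits), against 700 planned.

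**3. Time.** 12 December 2013 to 30 November 2015 is 718 days, or 23.6 months; 12.4 remain. Observed rate 10/23.6 = 0.42 per month. Required rate 240/12.4 = 19.3 per month, about 46 times the observed rate. A tenfold acceleration gives 10 + 10 × 0.424 × 12.4 ≈ 63.

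**4. Attainable sizes.** The constant rate is 10/23.59 × 36 = 15.3 (12.5 to 19.7 with Poisson limits on the observed rate). A linearly rising rate makes cumulative enrolment quadratic: 10 × (36/23.59)² = 23.3. The two extended scenarios apply the observed mix: 450 × 10/94 = 47.9 and 700 × 10/104 = 67.3.

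| Assumption | del(5q) n | 95 % interval at 57 % | Past 3 cycles |
|---|---|---|---|
| 36 months, constant rate | 15 | 0.32 to 0.82 | 8 |
| 36 months, linear ramp | 23 | 0.37 to 0.77 | 12 |
| Extended until non-del(5q) reaches 450 | 48 (22 to 92) | 0.43 to 0.71 | 24 |
| Extended to 700 lower-risk, any mix | 67 (33 to 119) | 0.45 to 0.69 | 34 |
| As stated | 250 | 0.51 to 0.63 | 125 |

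The ranges in brackets use the exact limits of the 9.6 % share. Wald intervals are rough at n = 15; Wilson gives 0.33 to 0.78 there.

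**5. How long the extended scenarios take.** At constant rates, 450 non-del(5q) patients take 450/(94/23.59) ≈ 113 months, and 700 lower-risk patients take 700/(104/23.59) ≈ 159 months. Neither fits in 36.

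**6. Whole registry.** 306/23.59 × 36 = 467 at a constant rate, and 306 × (36/23.59)² = 713 on a linear ramp, against about 1500.

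**The case against.** - **A target and an interim count are different things.** The sample-size text states design assumptions, the interval is correct for its n, and sizes and durations are given as approximate. This stands: there is no calculation error. But approximate does not stretch from 250 to 15 or 23.
- **Consecutive enrolment does not cap del(5q) at about 48.** A reader might infer that the rule by itself makes 250 impossible. It does not: the non-del(5q) subcohort could close at 450 while del(5q) stays open. What rules this out is the enrolment period. At the observed rate the remaining 240 patients would take 240/0.424 ≈ 566 months, about 47 years.
- **The time projections are extrapolations.** Site-activation dates are not given, so the average rate may understate later accrual. This stands, and it is why ranges are needed. It does not touch the case mix, and nearly all planned sites were already active.
- **An enrichment plan may sit in the full protocol.** It may, and its absence from an article is not the point here. The point is that the stated size and window do not fit the stated counts.
- **This is a descriptive registry.** No decision rule depends on the interval, so the harm is a wider interval that the final n will reveal. That limits the consequence but does not make the stated precision right.

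**Conclusion.** The concern holds as a mismatch between the stated del(5q) size and the registry's own accrual within 3 years. On the counts given, month 36 brings about 15 to 23 del(5q) patients, an interval half-width of about 0.20 to 0.25 instead of 0.06, and about 8 to 12 patients past 3 cycles instead of 125. Even the most generous extended scenario in the table has an upper limit of 119. These figures rest on 10 del(5q) patients, an unknown activation schedule and an enrolment clock that starts with the first patient.

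Three stronger readings are not supported:

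- About 50 should not be adopted as the achievable size. It needs 450 non-del(5q) patients, which takes about 113 months at the observed rate.
- A reader might infer that the lower-risk response estimate is already distorted by over-representing del(5q). The article gives the two subcohorts separate response rates and names them separately in its objectives, and no quota sampling is described. That risk arises only if 250 is pursued by targeted enrolment and the subcohorts are then pooled.
- The cohort counts under Status add to 305, not 306. This is clerical and has no bearing here.

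**What to change.** In Sample size, replace the single del(5q) interval and the figure of 125 with a short table of attainable sizes, each tied to its assumption, as in the working. Give the projections as ranges, and say that they rest on 10 patients.

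In Data collection, restate the enrolment period and total duration to match the scenario chosen, since total enrolment projects to about 467 to 713 of 1500 at month 36.

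If 250 is kept through targeted del(5q) enrolment, state this in Data quality as an exception to the consecutive-patient rule, and do not present the pooled lower-risk cohort as representative unless it is weighted to the consecutive-patient mix.

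Cost: a change of text in two or three sections and less favourable stated precision. Restating the figures needs no extra patients. Extending accrual or targeting enrolment has operational costs that the article does not allow one to estimate.

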### Participants

Patients with newly diagnosed primary or secondary MDS or AML, according to the 2008 revised World Health Organization criteria [6], or ICUS as defined by Valent et al. [8] are eligible for inclusion. Patients do not have to receive treatment to participate. Disease diagnosis must (1) be confirmed by independent central eligibility review of clinical diagnostic reports of bone marrow aspirates and biopsies, cytogenetic analyses, molecular testing, and laboratory results and (2) occur ≤ 60 days prior to giving informed consent. Cohort assignment, including IPSS risk for patients with MDS, will be confirmed by central review. Reports of bone marrow aspirates or biopsies must be available for patients with MDS or ICUS but not those with AML if the laboratory results show ≥ 20 % blasts in the peripheral blood. Patients with MDS or ICUS must be ≥ 18 years of age, and patients with AML must be ≥ 55 years of age. Patients with suspected or proven acute promyelocytic leukemia are excluded because these patients benefit from treatment with distinct regimens that lead to favorable outcomes [21]. Patients with MDS or ICUS previously treated with disease-modifying agents, including prior cytotoxic agents for MDS (drugs for other cancers are allowed), azacitidine, decitabine, lenalidomide, or targeted therapies (eg, FLT3 inhibitors), are excluded. Patients with AML can have initiated treatment with active agents within 14 days prior to providing informed consent. Prior use of supportive care, such as transfusions, antibiotics, iron chelators, erythropoiesis-stimulating agents or other hematopoietic growth factors, and tumor lysis prophylaxis is allowed. Patients with AML secondary to MDS could have received prior therapy with active agents for treatment of MDS. All patients must also be willing and able to complete the enrollment and follow-up PRO instruments in English or Spanish.

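### The response-rate intervals and the 122 expected responders hold only if every enrolled lower-risk MDS patient starts the drug, which the protocol itself does not expect

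*Protocol article*

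**What the plan says.** The Sample size section splits the lower-risk MDS cohort of 700; it "is divided into subcohorts of patients with del(5q) (n = 250) and without del(5q) (n = 450").

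For del(5q) the response rate is tied to a drug and dose: "For the 250 del(5q) patients with an expected response rate of 57 % with a 10-mg dose, based on the MDS-003 and MDS-004 studies". The section then says that "the 2-sided 95 % confidence interval for this estimate is 0.51 to 0.63".

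For non-del(5q), a sentence citing the MDS-005 study says that "approximately 270 patients, are expected to complete 4 cycles of therapy". An expected response rate of 27% follows, with the interval and conclusion given as "0.23 to 0.31 and 122 patients are expected to respond, providing enough patients to explore predictors of response".

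Three other places describe who will be treated:

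- Participants: "Patients do not have to receive treatment to participate".
- Background: asymptomatic lower-risk MDS is often handled by a watch-and-wait "approach, without specific therapy". Symptomatic lower-risk patients generally receive supportive care or lenalidomide.
- Data collection: the registry is non-interventional, and treatment decisions rest with the clinician.

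No section gives the share of either subcohort expected to start the drug.

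**The concern.** A response rate observed in treated patients describes people who receive the treatment. Its precision in the registry depends on how many registry patients start that treatment, not on how many enrol. The Sample size section uses enrolment as the denominator, although the rest of the article describes a cohort in which some patients will be untreated and others will receive something else.

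These are the only calculations behind any cohort size. The higher-risk MDS and AML sizes are asserted to be adequate, and no estimation was done for ICUS. Treatment outcomes by del(5q) status are part of a primary objective. The conclusion that predictors of response can be explored rests directly on the count of 122. If uptake is well below 100%, the intervals are wider than stated and the predictor analysis has far fewer responders to work with.

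**Working it through.** **Inputs from the Sample size section.** del(5q): n = 250, p = 0.57, stated interval 0.51 to 0.63. Non-del(5q): n = 450, p = 0.27, stated interval 0.23 to 0.31, 122 responders. Two-sided 95% level.

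**Input not in the document.** The share f of each subcohort that starts the drug. It is an assumption here, shown at 75%, 50% and 25% beside the 100% case.

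**Step 1: reproduce the stated figures.** Normal-approximation interval, p ± 1.96 × √(p(1 − p)/n):

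- del(5q): 0.57 ± 1.96 × √(0.57 × 0.43/250) = 0.57 ± 0.061, that is 0.509 to 0.631. This matches.
- Non-del(5q): 0.27 ± 1.96 × √(0.27 × 0.73/450) = 0.27 ± 0.041, that is 0.229 to 0.311. This matches.
- Responders: 0.27 × 450 = 121.5, about 122. This matches.

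The denominators are therefore the full enrolled subcohorts, which amounts to f = 100%.

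**Step 2: vary uptake.** The number of starters is f × 250 or f × 450. The half-width grows by a factor 1/√f, and the responder count falls in proportion to f.

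| Uptake f | del(5q) starters | 95% interval (half-width) | Non-del(5q) starters | 95% interval (half-width) | Non-del(5q) responders |
|---|---|---|---|---|---|
| 100% (as stated) | 250 | 0.51–0.63 (0.061) | 450 | 0.23–0.31 (0.041) | 122 |
| 75% | 187.5 | 0.50–0.64 (0.071) | 337.5 | 0.22–0.32 (0.047) | 91 |
| 50% | 125 | 0.48–0.66 (0.087) | 225 | 0.21–0.33 (0.058) | 61 |
| 25% | 62.5 | 0.45–0.69 (0.123) | 112.5 | 0.19–0.35 (0.082) | 30 |

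At 50% uptake the half-widths are √2 ≈ 1.41 times those stated; at 25% they double.

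**Step 3: could the enrolled denominator be kept?** Only if the estimand were the proportion of all enrolled patients who respond to the drug, and then 57% and 27% would no longer be the expected values. With half of the del(5q) patients starting and the rest counted as non-responders, the expected proportion would be 0.5 × 0.57 = 0.285. The pairing of an on-treatment rate with an all-enrolled denominator is consistent only at f = 100%.

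**Step 4: what the 125 and 270 are.** For del(5q) the section says: "Therefore, the expectation is that 125 patients will be on lenalidomide for more than 3 cycles". This is 0.50 × 250 = 125. The non-del(5q) count is 0.60 × 450 = 270. Both count patients who stay on therapy to a given cycle, and both are percentages of full enrolment, so they also take every enrolled patient as a starter. They are not the number treated. The 125 del(5q) starters in the 50% row agree with the first of them only by coincidence.

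**The case against.** The strongest defence is that this is a mainly descriptive observational registry. Cohort sizes were chosen for adequate representation, no power claim depends on these intervals, and the predictor aim is only exploratory. The analysis denominator is commonly set in the SAP, and at moderate uptake the intervals remain usable: at 75% the half-widths rise only from 6.1 to 7.1 points and from 4.1 to 4.7 points. That much stands, and it limits the consequence. It does not rescue the text, because the article states particular intervals, a responder count and an adequacy conclusion, and all of them need an uptake that its own description of the cohort excludes.

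A reader might infer more than the document supports:

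- *That 125 and 270 are the treated patients, so that 0.48 to 0.66 and about 73 responders (0.27 × 270) are the corrected values or bounds.* They count patients continuing, not starting. A response rate among treated patients uses starters, and a patient who responds and stops early still counts. Nor are these figures bounds: 75% uptake gives a narrower del(5q) interval and about 91 non-del(5q) responders, while 25% uptake gives worse on both.
- *That the section contradicts itself because 57% of 250 is about 143 responders, more than the 125 staying past 3 cycles.* A patient can respond and then stop, so the two counts are compatible.
- *That the 27% is stated to be a lenalidomide rate.* The section names lenalidomide only for del(5q). The 27% follows the sentence on MDS-005 and cycles of therapy, which makes it an on-treatment rate, but the drug is not named. The denominator problem is the same whichever drug it is.
- *That the sums are wrong.* They are right; the fault is an unstated assumption about the denominator.

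**Conclusion.** The concern holds as a denominator fault. The intervals 0.51 to 0.63 and 0.23 to 0.31 and the count of 122 are best-case values that require every enrolled lower-risk patient to start the drug. The Participants, Background and Data collection sections contradict that. The size of the overstatement cannot be fixed from the document because uptake is not given. Over assumed uptake of 75% to 25%, the del(5q) half-width goes from 7.1 to 12.3 points against 6.1 stated, the non-del(5q) half-width from 4.7 to 8.2 points against 4.1, and expected non-del(5q) responders from about 91 to about 30 against 122. The claim of enough responders to explore predictors is affected most. These figures assume that the 57% and 27% apply unchanged to registry patients who start the therapy, and they use the same normal approximation that reproduces the plan's own intervals.

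**What to change.** In the Sample size section:

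1. State that response rates are estimated among patients who start the therapy concerned, and name that therapy for the 27%.
2. Give the expected number of starters in each subcohort and its basis.
3. Replace the single intervals and the 122 with a short table over uptake, such as the one above, with the present figures labelled as the 100% case.
4. Keep 125 and 270 as counts of patients continuing on therapy, and do not use them as the treated denominator.
5. Tie the scope of the exploratory predictor analysis to the number of responders expected under that table.

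This is a change of text only; enrolment targets and data collection need not change. The one cost is that the stated precision and responder count become less favourable.
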